### Efficacy measurements

The primary efficacy measurements are the ADAS-cog [20] and the Clinician Interview-Based Impression of Change (CIBIC-plus) [21]. The ADAS-cog contains 12 items dealing with word recall, naming objects and fingers, commands, constructions and ideational praxis, orientation, word recognition, spoken language ability and comprehension of spoken language, word-finding difficulty, and attention. The scores of the ADAS-cog range from 0 to 75, and a higher score indicates higher impairment.

The CIBIC-plus is used to assess the global clinical status of the demented patient relative to baseline based on information from a semi-structured interview with the patient and the caregiver, and was designed specifically to evaluate the severity of cognitive dysfunctions characteristic of AD patients [21]. The score of the CIBIC-plus ranges from 1 to 7; a score of 1–3 indicates improvement, 4 means no change, and 5–7 indicates decline.

The secondary efficacy measurements include the MMSE and ADL [19]. The MMSE is used to assess the extent of cognitive dysfunction. The ADL mainly will be used to measure the basic activities and the instrumental activities of daily living. The ADL scale can be divided into the Physical Self-Maintenance Scale (PSMS) and the Instrumental Activities of Daily Living (IADL). The PSMS relates to physical activities, such as toileting, mobility, dressing, and bathing; the IADL contains eight items, such as shopping, cooking, doing laundry, handling finances, using the telephone, mode of transportation, responsibility for own medication, and housekeeping.

### Safety assessment

Studies have reported that the adverse events of FFDS tablets were as follows [22]: a total of 11 patients suffered adverse events. Five patients suffered allergic reactions, such as rash or allergic asthma; two patients suffered hypokalemia, with symptoms like bloating and fatigue; one patient also showed significant sinus bradycardia, one patient showed tuberculosis hemoptysis, one showed thrombocytopenia, and one patient suffered hematuria with back pain and fever.

Safety will be assessed at baseline (week 0), mid-study (week 12), and at the end of treatment (week 24). The safety assessment will include the following: (1) physical examination of vital signs, including breathing, heart rate, and blood pressure; (2) electrocardiography; (3) laboratory testing, including urine and blood; and (4) any adverse events that may occur, including the types of adverse events, time of occurrence, duration, treatment measures, and evaluation of the correlation between the tested drugs and the adverse event (positive, probable, possible, or not correlated); the severity of the adverse event (mild, moderate, and severe) must be evaluated. A mild adverse event is described as one that could induce mild symptoms, but the symptoms could be well tolerated, and there is no necessity to receive treatment or discontinue the study drugs. A moderate adverse event is defined as symptoms that could not be well tolerated and could affect the subject’s ADLs; a moderate adverse event means that the tested drug must be stopped. Severe adverse events include any event that is fatal, considered to be life-threatening, or requires hospitalization.

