**Fig. 1 Fig1:**
[figure not shown]
Schedule of enrollment. *ITT* intent to treat

The neuropsychological assessments, laboratory determinations, measurements of vital signs (including temperature, blood pressure, and electrocardiogram), and neurological tests (including an examination of cranial nerves, motor coordination, muscle tonus, and power) will be evaluated before patients are enrolled. The diagnosis of probable VaD will be based on the neurological test and confirmed by the criteria of the NIND-AIREN and DSM-IV, the HIS, and the Hamilton Depression Rating Scale (HAMD) [18]. For differential diagnosis, the Activities of Daily Living (ADL) [19] and a scan of the brain are also necessary.

All patients will receive an assessment at baseline (0 week), 12 weeks, and 24 weeks, and an additional assessment will be performed 12 weeks after completing the assigned double-blind medication. The study timeline and endpoints are shown in Table 1.

**Table 1 Tab1:** Study timeline and endpoints

Items	−2 weeks (run-in)	0 week (baseline)	12 weeks (mid-term follow-up)	24 weeks (endpoint)	36 weeks (follow-up)
Inclusion criteria		√			
Exclusion criteria		√			
MRI scan	√				
Informed consent	√				
General information	√				
Vital signs	√	√	√	√	√
MMSE	√	√	√	√	√
HAMD	√				
HIS	√				
ADAS-cog		√	√	√	√
CIBIS		√			
CIBIC-plus			√	√	√
ADL		√	√	√	√
Safety measure		√	√	√	
Adverse event		√	√	√	
Concomitant drugs		√	√	√	√

*CIBIS* Clinician Interview-Based Impression of Severity, *CIBIC-plus* Clinician Interview-Based Impression of Change

Any adverse events will be recorded during the duration of the trial. Patients will receive four clinical assessments.

Patients, caregivers, the study investigator, any other personnel involved in the study, and the investigating staff of the Hutchison Whampoa Guangzhou Baiyunshan Chinese Medicine Company Limited will remain blinded until all patients complete the study and all data are collected.

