### Statistical analysis

Statistical analyses will be conducted in three populations. The intent-to-treat (ITT) population will consist of all of the randomized population who take at least one dose of medication and at least one primary efficacy evaluation on treatment. The fully evaluated (FE) population will include all randomized patients who have received at least 80 % of the assigned 24 weeks of double-blind medication with a complete record of efficacy variables, with no major protocol violations. The safety set (SS) population will include all of the randomized population who receive at least one dose of the study medication, with at least one safety record post baseline.

The efficacy analysis will be conducted with the ITT and FE populations. The ADAS-cog and CIBIC-plus will be analyzed using the last observation carried forward (LOCF) method for the replacement of missing observations. The ADAS-cog and MMSE will be assessed by analysis of covariance (ANCOVA) with baseline scores as covariates and the treatment group and center as factors. The Cochran–Mantel–Haenszel test will be used for CIBIC-plus scores. The occurrence of adverse events will be analyzed using frequency calculations and descriptive statistics.

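### The text records adverse events for the whole trial, but Table 1 and the Safety assessment section end their collection at week 24, leaving the week-36 visit without a harms enquiry

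*Protocol article*

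**What the plan says.** Three places in the protocol article set the period over which harms are collected.

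- **Procedures, text around Table 1.** Patients are assessed at weeks 0, 12 and 24, and "an additional assessment will be performed 12 weeks after completing the assigned double-blind medication". Below the table: "Any adverse events will be recorded during the duration of the trial". The next sentence reads "Patients will receive four clinical assessments".
- **Table 1.** The *Adverse event* and *Safety measure* rows are ticked at weeks 0, 12 and 24. In the column headed "36 weeks (follow-up") both are blank, while vital signs, MMSE, ADAS-cog, CIBIC-plus, ADL and concomitant drugs are ticked.
- **Safety assessment.** "Safety will be assessed at baseline (week 0), mid-study (week 12), and at the end of treatment (week 24"). The fourth component of that assessment is "any adverse events that may occur, including the types of adverse events, time of occurrence, duration, treatment measures".

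The Statistical analysis section then limits the safety set to randomised patients who "receive at least one dose of the study medication, with at least one safety record post baseline". Adverse events are to be summarised by frequencies and descriptive statistics.

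**The concern.** The general statement and the visit schedule cannot both be followed. A site working from the general statement would ask about adverse events at week 36. A site working from Table 1 or the Safety assessment section would not. With six centres, ascertainment after treatment could differ by centre.

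Safety is a stated aim, and under Sample size calculations the number per group was raised from 88 to 100 expressly for safety. The safety results will be frequencies, so the collection window and the denominator determine what is reported. The window is stated inconsistently, and the denominator depends partly on whether a patient was followed up.

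**Working it through.** The plan states no figure on this point that could be reproduced. The check compares the passages and adds simple arithmetic.

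**1. Does the trial's duration include week 36?** The text lists weeks 0, 12 and 24 plus one assessment 12 weeks after the end of treatment: 24 + 12 = week 36. That makes four assessments, which matches the count given directly after the adverse-event sentence. On that reading the adverse-event rule reaches week 36.

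**2. Side by side.**

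| Source | Adverse events collected at or through |
|---|---|
| Procedures, text | whole trial, four assessments (to week 36) |
| Table 1 | weeks 0, 12, 24 |
| Safety assessment | weeks 0, 12, 24 |

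**3. Size of the gap if the table and the Safety section are followed.** Weeks after randomisation: 36. Weeks covered: 24. Uncovered: 36 − 24 = 12, and 12/36 = 33.3 %.

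**4. What is still collected at week 36.** Vital signs, which are component (1) of the safety assessment, and concomitant drugs are ticked. Safety capture at that visit is reduced, not absent.

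**5. Effect of the safety-set rule on an observed proportion.** Input from the plan: 120 patients per group. Assumption for illustration: 10 patients in an arm have a recorded adverse event. A recorded event after baseline is itself a safety record, so these 10 stay in the set, and the patients dropped have no recorded event. With *k* dropped, the observed proportion is 10/(120 − *k*):

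| *k* dropped | Calculation | Observed proportion |
|---|---|---|
| 0 | 10/120 | 8.3 % |
| 6 | 10/114 | 8.8 % |
| 12 | 10/108 | 9.3 % |
| 24 | 10/96 | 10.4 % |

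The last row is the extreme case in which the whole planned 20 % discontinuation (0.20 × 120 = 24) leaves no post-baseline record. The values of *k* span a range and are not estimates. The numerator is fixed and the denominator shrinks, so the rule raises the observed proportion.

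**The case against.** **The 24-week reading.** The Background and Discussion speak of a 24-week study, and Study design describes only the run-in and the 24-week treatment phase. On that view the adverse-event sentence could mean the treatment period alone, and there would be no conflict. This reading fits poorly with the next sentence, which counts four assessments and so includes week 36. Even if it were intended, the wording would need to say so.

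**Post-treatment events are not shown to be lost.** This stands. If the general statement governs, they are recorded. The 33 % gap arises only where sites follow the table and the Safety section. Events between weeks 12 and 24 are covered by the week-24 assessment in any case.

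**The safety set.** A reader might infer that it undercounts harms, because a dosed patient who leaves before week 12 drops out of the set. The documents do not support that inference. They do not restrict a safety record to a scheduled visit, and the Compliance strategy section provides a telephone line and calls to patients lost to follow-up. A patient with a recorded post-baseline event stays in the set. Undercounting would follow only if the term meant a scheduled week-12 or week-24 assessment, which the article does not say. The article also gives no rate of loss before week 12, so the number excluded cannot be estimated from it.

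**Convention and cost.** Requiring a post-baseline record is a known convention for a safety set, so that half of the point is secondary. Study design requires renewed ethics approval for any amendment, and Trial status reports 212 subjects already in the study, so a change now would give mixed collection windows. Both costs are real but small.

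**Conclusion.** The contradiction on the adverse-event window is explicit and should be corrected. Both versions are stated, so it is not a detail left out by condensing a protocol into an article. If sites follow Table 1 and the Safety assessment section, adverse events in 12 of 36 post-randomisation weeks (33 %) are not systematically collected, although the patient attends a visit at the end of that period. How many events this would affect cannot be derived from the document.

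The safety-set condition is a lesser matter. Requiring "with at least one safety record post baseline" makes membership depend on follow-up rather than on exposure, and exclusions could differ between arms. The proportion among recorded events would rise, not fall. Because any events in the excluded patients are unobserved, the direction of the overall bias is unknown.

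Neither point affects power or the efficacy analyses.

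**What to change.** 1. Tick *Adverse event* at week 36 in Table 1, and extend the adverse-event item of the Safety assessment section to week 36, in line with the general statement under Procedures. If laboratory tests and other safety measures are meant to end at week 24, say so separately.
2. Report on-treatment events (to week 24) and post-treatment events (weeks 24 to 36) separately, so that the longer window does not blur the comparison on treatment.
3. Define the safety set as all randomised patients with at least one dose. If the post-baseline condition is kept, state what counts as a safety record and report the number of dosed patients excluded in each arm.

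**Cost.** One table cell, a sentence in the Safety section and a short enquiry at a visit that already takes place, plus an ethics amendment. Patients already past week 36 can be covered only from source notes, so post-treatment coverage will be incomplete and the report should say for how many.

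### The printed mild, moderate and severe grades for adverse events do not form one scale: severe is described by seriousness outcomes, and some non-serious events fit no grade.

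*Protocol article*

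**What the plan says.** In the protocol article, section Safety assessment, grading is compulsory: "the severity of the adverse event (mild, moderate, and severe) must be evaluated". Wording is then printed for all three grades.

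- **Mild:** an event with mild symptoms, "but the symptoms could be well tolerated, and there is no necessity to receive treatment or discontinue the study drugs".
- **Moderate:** "A moderate adverse event is defined as symptoms that could not be well tolerated", with a possible effect on the patient's activities of daily living (ADLs). A moderate grade obliges the study drug to be stopped.
- **Severe:** "Severe adverse events include any event that is fatal, considered to be life-threatening, or requires hospitalization".

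No intensity criterion is printed for severe, and the article defines no separate category of serious adverse event. The same section asks for other details of each event, "including the types of adverse events, time of occurrence, duration, treatment measures" among them, and collects electrocardiograms and laboratory results. On analysis, the section Statistical analysis says: "The occurrence of adverse events will be analyzed using frequency calculations and descriptive statistics".

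**The concern.** Severity (how intense an event is) and seriousness (what outcome it has) are different attributes. Here the lower two grades describe mostly the first and the top grade only the second. An investigator who must choose one of the three would then be answering different questions at different levels, and for some events no answer is printed.

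Two things are at stake. Any summary of events by grade would mix intensity with outcome. And since the moderate grade triggers stopping of the drug, an event that cannot be graded leaves the investigator without a clear printed instruction on dosing. Safety and tolerability are stated aims of the trial, and the section Sample size calculations gives safety as the reason for going from 88 to 100 patients per group, so the grading rule deserves to be sound.

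**Working it through.** No figure in the plan depends on this point, so there is none to reproduce. The check is to apply the printed definitions to every type of event.

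**Step 1: events that meet a severe descriptor.** The severe sentence covers any event with one of its three outcomes, with no condition on symptoms. A low-intensity event that needs a hospital stay, for example for monitoring, is therefore severe.

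**Step 2: events that meet none of the severe descriptors.** The mild and moderate wording uses three yes/no attributes: well tolerated (T), needs treatment or discontinuation (R), affects ADLs (A). That gives 2 × 2 × 2 = 8 combinations. Mild needs T = yes and R = no, and says nothing on A. Moderate needs T = no and A = yes, and says nothing on R as a condition.

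| T | R | A | Printed grade |
|---|---|---|---|
| yes | no | no | mild |
| yes | no | yes | mild |
| no | no | yes | moderate |
| no | yes | yes | moderate |
| yes | yes | no | none |
| yes | yes | yes | none |
| no | no | no | none |
| no | yes | no | none |

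Mild covers 2, moderate covers 2, and 8 − 2 − 2 = 4 have no printed grade. Two of the four are tolerated events that need treatment or discontinuation; the other two are not tolerated but leave ADLs unaffected.

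**Step 3: sensitivity to reading.** Suppose the two conditions of moderate are read as alternatives (T = no or A = yes). Moderate then covers the 4 combinations with T = no and the 2 with T = yes and A = yes, 6 in all. One of these (T yes, R no, A yes) is then both mild and moderate, and one combination (T yes, R yes, A no) still has no grade. The gap for a tolerated, treated event without effect on ADLs survives either reading.

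**Step 4: a disabling event without admission.** It is not tolerated and affects ADLs, so the only printed wording it meets is moderate.

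**Step 5: are such events plausible here?** The earlier reports cited in Safety assessment list rash, hypokalemia, thrombocytopenia and sinus bradycardia as adverse events of these tablets. A tolerated rash that is treated falls in the gap. So would a laboratory or ECG abnormality without symptoms that is reported as an adverse event and treated without admission. The article gives no rates for this trial, so the number of affected events cannot be computed.

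**The case against.** The best defence has four parts.

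- **The list for severe is open.** The sentence says *include*, so a disabling event without admission may still be graded severe, and the full protocol may hold an intensity criterion. This stands. A reader might infer that such events will certainly be under-graded; the text supports only that they may be. The openness does not help an event of low intensity that needs a hospital stay, because an open list adds events and removes none.
- **Mild and moderate are not pure intensity grades.** Both carry an action: no treatment or discontinuation for mild, stopping the drug for moderate. The ladder is a hybrid throughout. This also stands, and the contrast should not be put as intensity against outcome alone. It does not close the gaps in the table.
- **ECG and laboratory tests are listed apart from adverse events.** The article does not say when a symptom-free result becomes a gradable event. This stands, so the point reaches only those findings that are reported as adverse events.
- **The consequences are modest.** The article promises no table by grade, the same definitions apply in both blinded arms, and details such as treatment given are recorded separately. This stands and sets the size of the point.

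A condensed article may leave detail to the full protocol, but here wording for all three grades is printed and grading is compulsory. The point concerns what is stated.

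**Conclusion.** The point holds and is minor. As printed, events needing a hospital stay are severe regardless of intensity, and 4 of 8 types of non-serious event have no grade (at least 1 of 8 on the looser reading of moderate). The drug-stopping instruction is unclear for those events. The effect is confined to grading, summaries by grade and that instruction; total event counts, efficacy and sample size are unaffected.

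This rests on a literal reading of the article; the full protocol and case report form are not shown.

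Two further inferences are not supported. One is that the safety comparison between arms is biased: nothing in the definitions differs by arm. The other is that correction would be mainly recoding of past events because 212 of the planned 240 subjects were already entered (Trial status). That figure counts subjects, not events. Treatment lasts 24 weeks and the trial was ongoing, so subjects already entered could still have new events.

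**What to change.** 1. Define mild, moderate and severe on one exhaustive scale of intensity and function, for example severe = prevents usual activities. Word it so that it covers tolerated events that need treatment or discontinuation, events not tolerated but without effect on ADLs, and any symptom-free laboratory or ECG finding reported as an adverse event.
2. Record seriousness (death, threat to life, hospital admission) as a separate yes/no item.
3. State the drug-stopping rule on its own, separate from the grade.
4. Regrade events already recorded, blinded and before the code is opened. The section Procedures says that patients, caregivers and study staff "will remain blinded until all patients complete the study and all data are collected", so there was room for this when the article was written. The record of treatment given can help to find tolerated but treated events; the other kinds would need source notes.

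The cost is reworded definitions, possibly one case report form field (the form may already have it), and some blinded regrading. The regrading will be incomplete where intensity, tolerability or admission was not written down.

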### Compliance strategy

To maximize subjects’ compliance, we will try to prevent dropouts by providing ongoing support to patients. A direct telephone line set up for this clinical trial will enable the study team to communicate personally with the patients. If a patient is lost to follow-up, we will call to ask the reason and attempt to schedule a meeting at the patient’s convenience.

### Statistical analysis

Statistical analyses will be conducted in three populations. The intent-to-treat (ITT) population will consist of all of the randomized population who take at least one dose of medication and at least one primary efficacy evaluation on treatment. The fully evaluated (FE) population will include all randomized patients who have received at least 80 % of the assigned 24 weeks of double-blind medication with a complete record of efficacy variables, with no major protocol violations. The safety set (SS) population will include all of the randomized population who receive at least one dose of the study medication, with at least one safety record post baseline.

The efficacy analysis will be conducted with the ITT and FE populations. The ADAS-cog and CIBIC-plus will be analyzed using the last observation carried forward (LOCF) method for the replacement of missing observations. The ADAS-cog and MMSE will be assessed by analysis of covariance (ANCOVA) with baseline scores as covariates and the treatment group and center as factors. The Cochran–Mantel–Haenszel test will be used for CIBIC-plus scores. The occurrence of adverse events will be analyzed using frequency calculations and descriptive statistics.

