### Sample size calculations

Because there are few studies on the treatment of VaD, the sample size was calculated based on data from a study of AD treatment using the Alzheimer’s Disease Assessment Scale-cognitive subscale (ADAS-cog) [17]. The previous study reported that patients who received donepezil (5 mg/day) showed a mean improvement of 0.67 ± 0.51; the patients who received the placebo showed a worse score of 1.82 points. Using a one-sided test with a significance level of 0.05 and power of 90 %, the minimum number was 88 per group to detect a difference of 1.5 points on the ADAS-cog. To achieve an adequate number to detect the safety of the FFDS tablets, the number of the patients was increased to 100 per group. Considering a greater rate of discontinuation of 20 %, the sample size was increased to 120 per group to ensure adequate patients to complete the study.

The randomization is stratified according to center using SAS statistical software (version 9.13) (SAS Institute Inc., Cary, NC, USA). Balanced randomization generated by SAS statistical software is carried out in three steps (in blocks of four) by a statistician with no access to information on the patients or physicians. Patients will be randomized in a ratio of 1:1 to receive the FFDS or placebo tablets. The randomized code is generated in the randomization process and sealed in an envelope. Statisticians assign the medication group according to the randomization code. Afterwards, the sealed randomization codes and each available medication number are sent out to each center. Blinding will be broken only if a patient’s trial medication requires specific emergency treatment. Once the blinding is broken, the patient will be managed as off-trial.

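### Carrying the last observation forward on both primary outcomes puts a week-12 score in place of week 24 for late dropouts; a model using both visits would be a cheap improvement

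*Protocol article*

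**What the plan says.** The Efficacy measurements section names ADAS-cog and CIBIC-plus as the primary measures and says of the ADAS-cog that "a higher score indicates higher impairment". The Statistical analysis section fixes the missing-data rule for both: "The ADAS-cog and CIBIC-plus will be analyzed using the last observation carried forward (LOCF) method for the replacement of missing observations". ADAS-cog then goes into an ANCOVA and CIBIC-plus into a Cochran–Mantel–Haenszel (CMH) test. No other missing-data method is stated.

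Four other statements bear on the rule:

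- **Visits.** Procedures and Table 1 schedule efficacy assessments at weeks 0, 12, 24 (the endpoint) and 36 (after treatment).
- **Analysis sets.** ITT requires at least one dose and at least one primary efficacy evaluation on treatment. The fully evaluated (FE) set requires 80 % of medication, complete efficacy records and no major violation.
- **Dropout.** Sample size calculations: "Considering a greater rate of discontinuation of 20 %, the sample size was increased to 120 per group".
- **Expected course.** The same section takes its planning data from a study of Alzheimer's disease (AD), in which "the patients who received the placebo showed a worse score of 1.82 points".

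**The concern.** LOCF assumes that nothing changes after the last visit. The article's planning figures point the other way: the placebo patients it cites got worse. The Background also criticises the earlier phase II trial because its 12-week follow-up was too short to detect drug effects. LOCF puts that same 12-week outcome into the 24-week endpoint for each patient who leaves in the second half.

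A frozen week-12 score hides any later worsening. If the arms differ in late dropout, the between-arm difference then partly reflects who left. If they do not differ, an effect that builds up over 24 weeks is understated. The imputed values also enter the analysis as if measured. The rule governs both primary results.

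**Working it through.** **1. The plan's own figure, and the SD.** The article says "the minimum number was 88 per group to detect a difference of 1.5 points on the ADAS-cog", at one-sided 0.05 and 90 % power. The formula is n = 2 × (1.645 + 1.282)² × SD² / 1.5². The only printed spread is in "showed a mean improvement of 0.67 ± 0.51", not labelled as SD or SE. Used as an SD, 0.51 gives 2 per group, so 88 does not follow from the printed inputs. Solving for SD gives 1.5 × √(88/2) / 2.926 = 3.40. I use 3.4 as an assumption; it is not printed.

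**2. What gets carried.** ITT needs an on-treatment evaluation, and the first scheduled one is week 12. Patients who leave earlier therefore normally drop out of ITT. If all planned dropout came after week 12, up to 0.20 × 120 = 24 patients per arm would have a carried week-24 value.

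**3. Size per carried value.** Assume the 1.82 points accrue linearly over 24 weeks in both arms (no treatment effect). Half is present at week 12, so each carried value omits 1.82 / 2 = 0.91 points of worsening. The bias under the null is 0.91 × (difference between arms in the share of analysed patients with a carried value).

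**4. Under the null, all dropout after week 12.** SE = 3.4 × √(2/120) = 0.439. One-sided error = P(Z > 1.645 − bias/SE).

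| FFDS v placebo dropout | Bias (points) | One-sided error |
|---|---|---|
| 20 v 20 % | 0 | 5 % |
| 25 v 15 % | 0.91 × 0.10 = 0.09, for FFDS | about 7 % |
| 30 v 10 % | 0.91 × 0.20 = 0.18, for FFDS | about 11 % |
| 10 v 30 % | 0.18, against FFDS | 2 % |

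Simulation with 20,000 runs per setting (within-patient correlation 0.6) gave 4.9 %, 7.2 % and 10.9 % for the first three rows.

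**5. Half the dropout before week 12.** For 30 v 10 %, the early half leaves ITT, so 102 and 114 patients are analysed. The carried shares are 15/85 = 0.176 and 5/95 = 0.053. Bias = 0.91 × 0.124 = 0.11 points. SE = 3.4 × √(1/102 + 1/114) = 0.463, and the error is about 8 %. For 25 v 15 % the same steps give about 0.06 points and 6.4 %.

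**6. Other inputs.** With SD 6 and all dropout late, 30 v 10 % gives about 8 %. With a 3-point decline and SD 3.4, it gives 0.30 points and about 17 %.

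**7. With a true effect.** Take 1.5 points at week 24, half of it present at week 12, and 20 % late dropout in each arm. LOCF estimates 0.8 × 1.5 + 0.2 × 0.75 = 1.35, a loss of 10 %. Power at 120 per arm is about 92 %.

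**8. CIBIC-plus.** The mechanism is the same: a week-12 rating of no change stays in place whatever happens later. The article gives nothing from which to size this.

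**The case against.** The strongest reply is that the harm may be small. With near-equal dropout the test keeps its level and the estimate errs low. Power under LOCF in step 7 is about the same as for a completers analysis of 96 per arm (92 %). This stands, and it limits the severity.

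The inputs are also thin. The 1.82 points come from an AD study, used because vascular dementia data were few, and the article gives no time span for them. The eligibility criteria mention stepwise progression, not linear decline. This also stands, so the figures show scale and are not forecasts.

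A reader might infer that LOCF will flatter FFDS because FFDS patients will stop more often. The documents do not support that. The Safety assessment rule that a moderate adverse event ends the study drug applies to both arms and does not say that assessments end. The listed adverse events have no denominator or comparator. The Compliance strategy describes efforts to re-contact lost patients.

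Nor does the arm with more dropout always look better. That requires patients in that arm to be worsening after week 12; in an improving arm, LOCF forgoes later gain.

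The planned FE analysis might reveal a LOCF distortion, since it uses complete records. But it also selects on adherence and absence of violations, so it is only a partial check.

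Finally, the simulated dropout was unrelated to outcome. In that setting even a completers analysis is unbiased, so good behaviour of a likelihood model there says nothing about outcome-dependent dropout.

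**Conclusion.** The point holds at moderate severity: it should be fixed, as a cheap improvement. LOCF is a rule the article itself fixes for both primary outcomes, so it is not a detail left to an unseen analysis plan. Its direction and size depend on a dropout pattern nobody knows in advance.

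Under the stated assumptions, plausible imbalance (25 v 15 %) moves the null comparison by 0.09 points or less and the one-sided error from 5 % to about 7 % at most. The 11 % figure needs threefold differential dropout, all of it after week 12, and should be read as an extreme case. Dilution with equal 20 % late dropout is 0.15 of 1.5 points. Confidence in the mechanism is high. Confidence in the sizes is lower, because linear decline, the 24-week span, SD 3.4 and the dropout timing are all assumed. A reader might conclude that the trial's primary result would be invalid under LOCF; the documents do not support that.

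**What to change.** Change the primary analyses before unblinding. The article reports the study as ongoing and says blinding is kept until all data are collected.

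- **ADAS-cog:** a mixed model for repeated measures on change at weeks 12 and 24, with treatment, visit, treatment-by-visit, centre and baseline, testing the week-24 treatment contrast.
- **CIBIC-plus:** multiple imputation followed by the CMH test already planned.
- **LOCF:** keep it for both outcomes as a sensitivity analysis.

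State that the new primary analyses assume data missing at random. They use visits already scheduled, so no new data are needed. The cost is revised analysis wording, a little more programming and less direct comparability with older LOCF trials, which the LOCF sensitivity analysis largely preserves.
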